**Figure 2 F2:**
[figure not shown]
Graphical display and formulas used to calculate time-weighted averages for hypocarbia, hypercarbia and overall time spent outside the CO_2_ target range. The formulas account for both the severity of the hypocarbia/hypercarbia and time spent under hypocarbia/above hypercarbia in the numerator, divided by the total time until censoring for each patient. CO_2_, carbon dioxide.

### Sample size

We aim to recruit a total of 60 patients, 30 per study arm. To determine the feasibility to progress to a larger trial, we define feasibility of adherence to the allocated ventilation mode (primary feasibility outcome) if two-thirds or more (≥67%) of patients are ventilated with the allocated mode during ≥80% of the time from randomisation until censoring. If 47 out of 60 patients are ventilated with the allocated mode for ≥80% of the study time, this would yield a feasibility of adherence of 78% with a one-sided lower 95% CI of 68%. A sample size of 60 participants will allow us to assess other feasibility outcomes and is considered sufficient to assess the variation and distribution of continuous physiological outcomes for future trials, based on previously published flat^17^,^20^ and stepped rules of thumb for pilot trials.^21^

### Data collection

There are two primary sources of data for this study: (1) data manually entered into REDCap and (2) the electronic medical record.

Data for documentation and monitoring purposes that require manual collection is related to screening, consenting, protocol deviations, and adverse events for reporting and monitoring purposes. These data are recorded using a short electronic Case Report Form (eCRF) in REDCap electronic data capture tools hosted at the University Children’s Hospital Zurich. The data are accessible only to the study team, are password-protected and backed up nightly to the servers of the University Children’s Hospital Zurich. These data will be used to calculate a subset of the secondary feasibility outcomes.

Data related to the intervention and physiological outcomes of the trial is captured digitally through the electronic health record. This has two advantages: (1) there is almost no data entry burden for study coordinators, physicians or nurses on the care team and (2) time series data can be collected at a much higher temporal resolution than what would be possible if done manually. Electronic data sources include: clinical information system (CGM Clinical – Phoenix), intensive care clinical information system (MetaVision), laboratory information system and hospital administration system (Hospis). In MetaVision, time series parameters are collected every minute. The following medical devices feed data directly into the intensive care information system: mechanical ventilator (Bellavista) for all ventilation-related parameters and ETCO_2_, transcutaneous CO_2_ monitor (Sentec), SpO_2_ monitor (Pulsoximeter Rad-87 Massimo). The clinical data warehouse team at the University Children’s Hospital Zurich extracts information from the participants’ electronic health record from randomisation to censoring as a comma-separated value file. In addition, the mandatory dataset for the Swiss Intensive Care registry (MDSi, https://www.sgi-ssmi.ch/de/datensatz.html) is also captured in the clinical data warehouse and helps describe the patient cohort. The following information is extracted by the clinical data warehouse team to describe the study population, to calculate the primary feasibility outcome, and the primary and secondary physiological outcomes:

Baseline characteristics, such as age, sex, height, weight, Paediatric Index of Mortality-2 (PIM-2),^22 23^ which indicates the risk of death as a percentage from 0 to 100 (the higher the percentage, the higher the risk) and is used as a proxy for overall severity of disease, main diagnosis, date and time of admission, start of ventilation and randomisation, arterial blood gas analysis, endotracheal tube size and cuff.Respiratory mechanics and intervention-related parameters during the study period, including PEEP, MAP, peak inspiratory pressure, respiratory rate, tidal volume, minute volume, inspiratory time, leakage percentage, fraction of inspired oxygen (FiO_2_) and SpO_2_Outcome-related parameters during the study period such as ventilation mode, ETCO_2_, transcutaneous CO_2_, date and time of extubation, discharge or death, inspired fraction of oxygen ratio (SpO_2_/FiO_2_), results of consecutive blood gas analyses and arterial partial pressure of oxygen and inspired fraction of oxygen ratio (PaO_2_/FiO_2_). Arterial blood gas analyses are planned to be obtained every 6 hours during the study period. If the arterial line is removed during the study period, blood gas analyses may be obtained preferably from a capillary sample.

To test the electronic patient data extraction procedures, we performed test extractions of the above parameters using retrospective data from the electronic health records of 60 patients with approved general consent. This allowed us to streamline data extraction and cleaning procedures before recruitment started. In addition, we will perform a manual data verification to validate the data extraction after enrolment of the first 2 to 10 patients.

### Statistical analysis plan

The primary analysis will be performed on an intention-to-treat cohort. In case patients participate in the trial multiple times, the unit of analysis will shift from individual patients to individual admissions. This distinction will be appropriately handled through multilevel analyses. Results will be presented as effect estimates and 95% CIs, without the inclusion of p values. While missing data imputation will not be performed, outliers management in time series data will be addressed through the application of kernel smoothing.^24^

We will use descriptive statistics to summarise patient characteristics, adverse events and the distribution of feasibility and physiological outcomes. Categorical variables will be described using frequencies and percentages, continuous variables following a normal distribution using mean and SD and non-normally distributed variables using median and IQR. Normality will be assessed graphically with plots (histograms and Q–Q plots).

The analysis of both primary and secondary feasibility outcomes will be descriptive.

To analyse the primary physiological outcome, we will calculate the mean difference in the proportion of time spent in normocarbia (outcome) between the two ventilation modes (explanatory variable) using a linear mixed-effects regression model if the outcome is normally distributed. The stratification variable (age group) will be included as a fixed effect, and admissions will be nested within patients to account for correlated observations from patients potentially included more than once in the study. If the outcome has a skewed distribution, we will use quantile regression, also adjusting for stratification. The study is not powered to detect differences in physiological outcomes between the two ventilation models. Secondary physiological outcomes will be calculated using time-weighted averages as described in figure 2.

For physiological outcomes, we will conduct a per-protocol analysis including patients with adhere to the assigned ventilation mode for 80% or more of the study time.

As sensitivity analysis, we will calculate physiological outcomes using individual target CO_2_ ranges manually entered into the electronic information system by prescribing physicians when available, instead of standard normocarbia ranges. We will also assess the robustness of the results by testing different kernel sizes for smoothing and also present crude (not smoothed) results.

Secondary analyses will explore triggers and factors associated with deviations from the assigned ventilation mode (if patients received a mechanical ventilation mode different from that assigned at randomisation). We will examine interactions with age for physiological outcomes using plots and likelihood ratio tests. We will assess agreement between PaCO_2_ and both ETCO_2_ and transcutaneous CO_2_ values around the time windows when blood gas analysis was performed.

Further details on the statistical analyses can be found in the online supplemental material (statistical analysis plan).

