### Study outcomes

This pilot study is designed to provide estimates of feasibility and physiological outcomes with high temporal resolution to assist in the planning of future trials.

The *primary feasibility outcome* is adherence to the assigned ventilation mode among enrolled patients, measured from randomisation to censoring (48 hours after randomisation, extubation, discharge from PICU, or death, whichever comes first) among enrolled patients. This is measured as the proportion of time under invasive ventilation spent in the assigned ventilation mode. Discontinuations from the assigned mode lasting 15 min or less are excluded. We set a threshold for adherence to the allocated mode of 80%, meaning that patients who are ventilated with the assigned mode during ≥80% of their time in the study are considered adherent.The *primary physiological outcome* is the proportion of time spent within the target CO_2_ range (normocarbia, defined as CO_2_≥35 mm Hg or 4.5 kPa and ≤45 mm Hg or 6 kPa) as measured by end-tidal CO_2_ (ETCO_2_) recorded by the ventilation device and transferred to the electronic health record system every minute from randomisation to censoring. This is calculated as the total number of minutes spent with ETCO_2_ within the target CO_2_ range divided by the total number of minutes ventilated from randomisation to censoring. Arterial blood gas analysis is the gold standard to assess ventilation; however, this is an invasive and intermittent measurement. Trends in ETCO_2_ are non-invasive, continuously available at bedside and serve as a proxy for changes in partial pressure of CO_2_ in arterial blood (PaCO_2_) in children and neonates.^15^*Secondary feasibility outcomes* describe recruitment and implementation aspects of the study (table 2). These include the number of patients who were screened, were missed, gave consent and were randomised and enrolled per month, reasons for protocol violations; and times from randomisation to protocol violation, from start of ventilation to screening, from start of ventilation to randomisation and from consent to randomisation. The technical feasibility of digital data extraction is assessed through the proportion of enrolled participants with complete primary and secondary outcome data extracted from the electronic patient records.*Secondary physiological outcomes* on hypocarbia, hypercarbia or both are calculated using time-weighted averages to account not only for the time spent outside the target CO_2_ range but also for the magnitude of the difference from the target CO_2_ range (table 2, figure 2). The oxygenation index measured using peripheral oxygen saturation (SpO_2_) and partial pressure of arterial oxygen (PaO_2_) are also secondary physiological outcomes. While ETCO_2_, transcutaneous CO_2_ and SpO_2_ are time series measurements, the PaCO_2_ and PaO_2_ are obtained from intermittent blood gas analyses. To assess the later intermittent measurements over study time, each value will be carried on until the time of the next measurement.^16^

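### The primary physiological model adjusts only for age stratum although a baseline arterial blood gas is extracted: valid, but it probably gives up some precision

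*Protocol article*

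**What the plan says.** The primary physiological outcome (Study outcomes) is the "total number of minutes spent with ETCO_2_ within the target CO_2_ range divided by the total number of minutes ventilated from randomisation to censoring". The range is two-sided, 4.5 to 6 kPa.

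In the Statistical analysis plan section, a linear mixed-effects model compares the ventilation modes. On adjustment it says "The stratification variable (age group) will be included as a fixed effect", and on clustering "admissions will be nested within patients to account for correlated observations from patients potentially included more than once in the study". The fallback reads: "If the outcome has a skewed distribution, we will use quantile regression, also adjusting for stratification". Neither model names a baseline CO2 term. The treatment comparison is reported as an estimate with a 95% CI and no p value.

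The Data collection section lists, among baseline characteristics, "start of ventilation and randomisation, arterial blood gas analysis, endotracheal tube size and cuff". An arterial line is an inclusion criterion. ETCO2 and ventilation mode appear only among study-period parameters, and the data warehouse "extracts information from the participants’ electronic health record from randomisation to censoring as a comma-separated value file". Further statistical detail is left to a supplementary analysis plan that is not shown.

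**The concern.** CO2 status at randomisation may well predict how long a patient later stays in range. Randomisation is stratified by age only, so the arms can differ by chance in baseline CO2, and a model without a baseline term cannot correct for that. If the baseline value is prognostic, the CI is wider than the data require. The pilot is meant to supply parameter estimates for later trials, and a baseline-adjusted residual SD and the baseline-outcome correlation would be useful inputs.

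**Working it through.** **The plan's own figure.** The only calculation behind N = 60 concerns adherence: 47/60 = 78.3%, with an exact (Clopper-Pearson) one-sided 95% lower limit of 67.8%. This agrees with the stated 78% and 68%. No SD, effect size or precision is given for the physiological outcome, so what follows is in units of the outcome SD within age stratum.

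**Inputs.** 30 per arm (Sample size section); two-sided 95% CI; independent observations, ignoring the few possible repeat admissions. The value of r (within stratum, in absolute size) is assumed over a range because the article gives none.

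**Stratum-only model.** SE = √(2/30) = 0.258 SD. With 57 degrees of freedom the half-width is 0.517 SD.

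**With one baseline covariate.** SE = 0.258 × √[(1 − r²) × 56/55], where 56/55 is the approximate price of estimating one more coefficient; 56 degrees of freedom.

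| r (assumed) | Half-width (SD) | Ratio to 0.517 |
|---|---|---|
| 0 | 0.522 | 1.009 |
| 0.1 | 0.519 | 1.004 |
| 0.2 | 0.511 | 0.989 |
| 0.3 | 0.498 | 0.963 |
| 0.5 | 0.452 | 0.874 |
| 0.7 | 0.373 | 0.721 |

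Adjustment breaks even between r = 0.1 and r = 0.2. Leaving out the 56/55 term, the equivalent sample size is 60/(1 − r²): 66 patients at r = 0.3 and 80 at r = 0.5.

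**Chance imbalance.** The difference in baseline means also has SE 0.258 SD. It exceeds 0.25 SD in about 33% of randomisations and 0.5 SD in about 5%. A 0.5 SD imbalance moves the unadjusted estimate by 0.5 × r SD: 0.15 SD at r = 0.3 and 0.25 SD at r = 0.5.

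**Form of the covariate.** Time inside a two-sided range need not rise or fall steadily with CO2. The middle of the range is (4.5 + 6)/2 = 5.25 kPa. An illustrative simulation assumed a between-patient SD of 0.8 kPa, a within-patient SD of 0.5 kPa, and a correlation of 0.5 to 0.7 between baseline and study-period mean:

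- Raw baseline CO2 as a linear term: r about 0 when the population mean is 5.25 kPa; 0.24 to 0.34 in absolute size at 4.9 or 5.6 kPa; 0.39 to 0.55 at a range limit.
- Absolute distance from 5.25 kPa: 0.21 to 0.57 throughout.

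A plain linear term could therefore gain nothing, whereas a distance term helped in every case tried. These values show the shape of the problem and are not estimates for this trial.

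**The case against.** The strongest reply is that nothing here is an error. Adjusting for the stratification factor is a sound analysis, and the CI already allows for chance imbalance. The article disclaims power for the physiological comparison, and progression rests on adherence, which no covariate touches. The supplementary analysis plan may already contain a baseline term. All of this stands, and it limits the point to an efficiency gain in a stated model.

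The size of r is also open. The collected value is arterial while the outcome is end-tidal, and the article itself plans to assess how well the two agree. Physicians may enter individual CO2 targets, so distance from the standard mid-range may not reflect distance from the target being pursued. The table applies to the linear model and does not carry over directly to quantile regression. There, a covariate also changes the quantity estimated, to a difference in conditional quantiles.

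Three stronger readings are tempting, and the article does not support them:

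- **That the estimate is biased.** Randomisation prevents that. An imbalance in one realised allocation is sampling error.
- **That baseline CO2 is known to be a strong predictor.** No correlation is reported, and at r near 0 adjustment costs slightly.
- **That pre-randomisation ETCO2 is thrown away.** The described extract is "electronic health record from randomisation to censoring", but baseline items such as start of ventilation are extracted as well, and nothing says the source records are deleted. Those minutes may also not exist for everyone: the 24-hour criterion is an upper limit on prior ventilation, and no minimum before randomisation is set.

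**Conclusion.** The point holds as a modest, low-cost improvement. The stated model and its fallback leave out a baseline value that should already be in the extract. The linear-model estimate is unbiased without it, but precision is probably lost: the 95% CI would be about 4% narrower at r = 0.3 and 13% narrower at r = 0.5, against about 1% wider at r = 0. These figures assume 30 independent patients per arm, a linear model, a covariate of suitable shape, and a baseline PaCO2 for nearly all patients. The article lists arterial blood gas analysis without naming PaCO2 or its timing, so that last assumption needs confirming.

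**What to change.** Before outcome data are analysed by arm, add a dated statement to the analysis plan, or confirm that it already contains one:

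- **Primary physiological outcome.** One baseline covariate in both the linear mixed model and the quantile-regression fallback: the absolute distance of the last pre-randomisation PaCO2 from 5.25 kPa, or a spline of PaCO2. Choose one form in advance and do not let the choice depend on which data turn out to be available.
- **Missing baseline.** A simple rule that keeps these patients in the intention-to-treat model, for example a missing indicator or mean fill. State it as an exception to the rule against imputation.
- **Reporting.** Give the stratum-only estimate alongside.
- **Secondary outcomes.** Use the matching baseline: a directional PaCO2 term for hypocarbia and for hypercarbia, and the baseline oxygenation index for OI and OSI where available. Mean airway pressure and FiO2 are listed only for the study period, so availability must be checked.
- **Optional.** Extend the extraction to pre-randomisation ETCO2 for supplementary use only.

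Enrolment ended on 18 September 2024, so only the analysis changes. If analysis by arm has begun, present the adjusted model as a labelled supplement. The cost is a short addition to the plan, one degree of freedom (more with a spline or a missing indicator), and the missing-baseline rule.

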### Ethics and dissemination

This study received its first ethical approval from the Cantonal Ethics Commission of Zurich on 6 February 2023 (Business Administration System for Ethics Committees ‘BASEC’ identification number 2022–00829). Substantial changes to the study setup and study organisation, the protocol and relevant study documents will be submitted to the ethics committee for approval before implementation. Written informed consent is obtained from parents or guardians or adolescents aged 14 years and older (online supplemental material file, information and consent form for parents). Trial and participant data are only accessible to authorised personnel who need the data to fulfil their duties within the scope of the study. Participants are coded with a unique participant identifier on the CRFs and other study-specific documents. Coding documents linking the participant’s personal information to unique study identifiers are kept in a password-protected Excel spreadsheet with limited access.

Study results will be disseminated using traditional (submission for publication in a peer-reviewed journal and presentations at conferences) and novel (social media, web or podcasts) formats. Information about the study is available on the PICU page of the University Children’s Hospital Zurich—Children’s Research Centre webpage (https://www.kispi.uzh.ch/forschungszentrum/forschungsgebiete/intensivmedizin-neonatologie-fzk). Participants are asked during the consent process if they would like to be informed of the results of this study and, if so, their email address is collected for the purpose of sharing relevant publications.

### Patient and public involvement

Patient and public involvement has not been implemented in this pilot study, which focuses on feasibility and mechanistic aspects rather than translation to clinical care at this stage. We fully recognise the importance of involving patient families in the early stages of the research plan. If this pilot trial is successful, we plan to involve patient representatives in the design of future larger follow-up trials, with a stronger focus on patient-centred outcomes and clinical implications.

### Monitoring and safety

Monitoring is performed according to the predefined monitoring plan of the Children’s Research Center of the University Children’s Hospital Zurich. The site initiation visit took place prior to the enrolment of any participants. There are three routine onsite monitoring visits (first as soon as possible after the enrolment of the first two participants, second after enrolment of 30 participants, third and close-out visit after enrolment of the last participant or in case of premature closure). The monitor reviews all informed consent forms and at least one complete review of the trial master file/investigator site file. Eligibility, primary endpoint, serious adverse events and protocol-specific safety parameters are reviewed for the first two trial participants and up to 20% of trial participants enrolled at the time of the visit, if available. Randomisation and allocation will be reviewed for at least 20% of trial participants.

The study design does not pose any serious additional risks to patients, as patients require the use of invasive mechanical ventilation due to their clinical situation, and both modes of invasive mechanical ventilation are part of accepted standard of care at the study site. Exemptions from expedited reporting are allowed when the serious adverse event is either a clear result of the underlying condition or a known complication of the condition. Because both interventions are currently used in paediatric critical clinical care, the following serious adverse events that may occur in mechanically ventilated critically ill patients are exempt from expedited reporting: pneumothorax, endotracheal tube obstruction, pneumonia, sepsis, cerebral oedema, seizures, stroke, intraventricular haemorrhage, cardiac failure, atelectasis, air leaks, pulmonary haemorrhage, subglottic stenosis, vocal cord injury and need for extracorporeal membrane oxygenation. Deaths cases will be reported. We will submit an annual safety report to the ethics committee. Because this is a pilot feasibility trial investigating two currently accepted and commonly used ventilation modes with a high anticipated safety profile and minimal associated risk, with a main focus on digital trial data extraction procedures, a formal data safety monitoring board was not considered necessary.

